# Robot-assisted rehabilitation of people with breast cancer developing upper limb lymphedema: protocol of a randomized controlled trial with a 6-month follow‑up

**DOI:** 10.1186/s13063-023-07778-z

**Published:** 2023-11-15

**Keywords:** Lymphedema, Rehabilitation, Disability, Machine, Jawbone

## Abstract

**Supplementary Information:**

The online version contains supplementary material available at 10.1186/s13063-023-07778-z.

## Introduction

Upper limb lymphedema (ULLy) is an external (and/or internal) manifestation of lymphatic system insufficiency and deranged lymph transport enduring for more than 3 months [1]. 

ULLy frequently affects people as a consequence of breast cancer (BC), being one of the most feared morbidities of this tumor [2].

ULLy is often underestimated despite diminished motor skills, mood, and cognitive-behavioral complaints negatively condition the health-related quality of life (HRQoL) of cancer persons with BC [2–7]. The breast is the more prevalent source for metastatic tumors to the jawbones in women (41%), further contributing to a decrease in the HrQoL of individuals affected by cancer [8, 9].

A rehabilitative approach based on manual therapy, compression bandages along with physical exercises is a common treatment for people with ULLy and usually involves manual lymphatic drainage massage along with elastocompressive therapy, mobilization, muscle strengthening, and stretching of the limb [10, 11].

Robot-assisted rehabilitation (RR) is a rapidly expanding field within human–robot interaction, focused on harnessing the capabilities of robots to assist and enhance human skills during task-centered interactions [12]. RR systems have a wide range of applications, including physical assistance in post-stroke rehabilitation and robotic prosthetics [12, 13] as well as cognitive training for individuals with dementia and Alzheimer’s disease [14, 15]. This interdisciplinary field brings together expertise from various domains and, unlike conventional assistive robotic systems that primarily aim to complete tasks on behalf of users, RR emphasizes training enhancing user skills through interactive experiences. Such instruments maximize the effectiveness and efficiency of training by providing personalized-targeted assistance thus creating an environment that motivates users to perform specific tasks and achieve their training goals [16]. Recent advancements in technologies have facilitated the integration of robots as assistive systems across diverse domains, including also healthcare and physical rehabilitation, mostly focusing on neurorehabilitation in stroke and neurodegenerative diseases. For instance, the iCONE robotic system [17] emerges as an innovative solution for upper limb rehabilitation. By leveraging the principles of RR, the iCONE system enhances the effectiveness and efficiency of therapy delivery. It combines cutting-edge technology, interactive exergames, real-time feedback, and cloud connectivity to provide intensive, engaging, and user-friendly therapy for individuals with upper limb impairments.

We hypothesize that individuals with ULLy due to BC and who undergo RR will experience significant improvements in HRQoL and reduced pain levels similar to or higher than those in the control group based on regular rehabilitation. Specifically, we expect that the RR group will demonstrate higher scores in LYMQoL assessments, and report lower pain scores. We also hypothesize that people with ULLy and who develop jawbone metastases from BC will experience similar or higher improvements as per the same outcome measures as above than those in the control group (an additional self-administered outcome measure as for the assessment of craniofacial disability will be additionally added, as outlined in the Methods).

## Methods

This protocol adheres to the requirements of the Standard Protocol Items: Recommendations for Intervention Trials (SPIRIT) guidelines.

### Trial design and study setting

A single-center, double-blind, two-arm, parallel-group, superiority, randomized controlled trial (RCT) including people with ULLy with 6 months follow-up will be conducted in a secondary care rehabilitation hospital.

### Eligibility criteria

The inclusion criteria will be stable secondary iatrogenic lymphedema with uni- or bilateral swelling of the upper limbs due to BC; age > 18 years; and fluency (i.e., ability to read and write) in Italian. Exclusion criteria will be comorbidities potentially provoking lymphedema (e.g., lipedema, obesity, heart/kidney failure); ongoing chemotherapy/radiotherapy; acute infection (e.g., lymphangitis); other active vascular diseases (e.g., thrombosis); open wounds in the affected limb; mental health/psychiatric deficits (Mini-Mental State Examination score < 24); and refusal to participate.

Inclusion and exclusion criteria will be ruled out based on case histories and routing imaging (e.g. MRI scan, CT scan, ultrasonography, or radioisotope-based lymphoscintigraphy). Any people taking advantage of workers’ compensation or who had formerly undergone regular rehabilitation as ULLy will be excluded.

The presence or absence of jawbone metastases as a consequence of a BC will not influence the inclusion criteria.

### Participants

Between October 2023 and December 2024, persons referring to a secondary care rehabilitation hospital, following an evaluation by two physiatrists coordinated by the principal investigator (PI), will be recruited at the point of care in respect of the inclusion criteria, receiving materials included in a booklet about the study. Participants will be required to declare their consent to participate in the study, and they will be assigned to one of the two treatment programs by the physiatrists. A list of treatment codes and an automatic assignment system to conceal the allocation will be generated and stored through MATLAB and the allocation will follow a permuted-block randomization procedure with a 1:1 rate (an identification number will be assigned to each participant and listed in the dataset; treatment allocation will be automatically generated and concealed by a randomization software). The random sequence will be then converted by the physiatrist in the list of participants assigned to each arm and provided to the physiotherapists and psychologist who will perform the treatment. In order to partially avoid a selection bias, physiatrists will strictly follow the inclusion and exclusion criteria and they will only perform the first evaluation of the participants. The PI will remain blind to the allocation. Personal and occupational variables will be collected for enrolled people.

The PI and whoever will carry out the analysis of the data will be blinded to treatment allocation. The physiotherapists, the psychologist, and the participants will not be blinded.

Research assistants will give additional information to participants, with the latter required to assert their compliance to whichever intervention they are randomly assigned to, and to be present at the follow-up evaluation.

In order to partially limit expectations and to lower crossover troubles, participants will not be told of the trial’s hypothesis but only informed the research was planned to evaluate two interventions as for the rehabilitation of ULLy due to BC whose role had not yet been established.

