### Outcomes

#### Primary outcome measure

The primary outcome measure will be the change from the baseline of the Function domain in the Lymphedema Quality of Life (LYMQOL) questionnaire [20, 21] at 10 weeks and after 6 months. The LYMQOL is a self-administered questionnaire consisting of 21 items. The first 20 items assess the impact of lymphedema on Health-Related Quality of Life (HRQoL) and are categorized into four domains: Function (items #1–3), Appearance (items #4–8), Symptoms (items #9–14), and Mood (items #15–20). Each item is rated on a 4-point scale, ranging from 1 (not at all) to 4 (a lot), with higher scores indicating lower HRQoL.

The scores of all items within that domain are summed and divided by the total number of questions answered, in order to calculate the total score for each domain. Additionally, item #21 assesses the overall HRQoL, using an 11-point numerical scale ranging from 0 (poor HRQoL) to 10 (excellent HRQoL). The four summary scores related to each domain will be computed according to the guidelines provided by Keeley and colleagues [20].

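### The trial is labelled double-blind although the participants who self-report the primary outcome are unblinded, and the enrolling physiatrists also handle the random sequence, which undermines the claimed concealment

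*Protocol article*

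**What the plan says.** **Blinding.** The protocol article, under Trial design and study setting, describes the study as "A single-center, double-blind, two-arm, parallel-group, superiority, randomized controlled trial (RCT"). Under Participants it says: "The PI and whoever will carry out the analysis of the data will be blinded to treatment allocation". The next sentence says: "The physiotherapists, the psychologist, and the participants will not be blinded". Under Primary outcome measure: "The LYMQOL is a self-administered questionnaire consisting of 21 items". The change from baseline in its Function domain, at 10 weeks and after 6 months, is the primary outcome. The secondary outcomes are the other LYMQOL domains, a pain rating scale and, for people with jawbone metastases, a craniofacial disability inventory. The participant answers all of them.

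**Allocation.** The Participants section gives the physiatrists several tasks. Candidates, "following an evaluation by two physiatrists coordinated by the principal investigator (PI), will be recruited at the point of care". After consent, "they will be assigned to one of the two treatment programs by the physiatrists". Then: "The random sequence will be then converted by the physiatrist in the list of participants assigned to each arm", and this list goes to the physiotherapists and psychologist who deliver treatment. The same section says that MATLAB generates and stores the treatment codes, that an automatic system conceals the allocation, and that the method is permuted blocks at 1:1. No block size is given. Its stated safeguard, which it describes as only partial, is that "physiatrists will strictly follow the inclusion and exclusion criteria and they will only perform the first evaluation of the participants".

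**The concern.** These are two separate faults, and both concern what the article states rather than what it leaves out.

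The first is the label. Double-blind tells a reader that expectation is unlikely to have shaped the outcome scores. Here the person scoring the primary outcome knows the arm. Expectation is a realistic worry because the robot program totals 60 hours against 30 for regular rehabilitation, a contact-time difference that the Discussion lists as a limitation. No objective limb measure appears among the primary or secondary outcomes to offset this.

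The second is who handles the sequence. Concealment works when the person deciding on eligibility cannot know or infer the next assignment. Some criteria leave room for judgement, such as whether lymphedema is stable or whether a comorbidity could provoke it. If the next arm is known or can be guessed, such judgements can be steered, even unconsciously. With 44 participants, a few steered enrolments could unbalance the arms in ways that no analysis can reliably repair.

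**Working it through.** The article gives no figure on this point to reproduce, so the first two steps compare the text and the third illustrates the size.

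**Step 1: blinding, role by role**

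| Role | Blinded? | Source |
|---|---|---|
| Participants (score the primary outcome) | No | Participants; Primary outcome measure |
| Physiotherapists, psychologist | No | Participants |
| PI | Yes | Participants |
| Data analyst | Yes | Participants |

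Neither the treated nor the treating parties are blind, and the outcome assessor is the unblinded participant. The label contradicts the description.

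**Step 2: allocation, task by task**

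| Task | Who |
|---|---|
| Evaluate candidates, apply criteria | Physiatrists |
| Generate, store and conceal the sequence | Software |
| Assign participants to a program | Physiatrists |
| Convert the sequence into the arm list | Physiatrist |
| Receive the list | Physiotherapists, psychologist |

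The software is said to conceal the sequence, but its output passes through the role that decides who enters. The statement that the physiatrists perform only the first evaluation does not help, because enrolment is exactly where foreknowledge matters. It also sits awkwardly with the Auditing section, where physiatrists audit at the end of treatment and follow-up.

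**Step 3: how predictable the next allocation could be**

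Inputs: 1:1 permuted blocks (Participants) and 44 recruited (Sample size and statistical analysis). Assumptions, none of them stated in the article: a fixed block size *b* of 2, 4, 6 or 8, known to the physiatrist, who also knows all past allocations but no future ones.

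An allocation is certain in advance when every slot left in the block belongs to one arm. The number of certain allocations in a block is therefore the length of its final run of identical assignments. Averaging over all equally likely orders:

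- *b* = 2: 2 orders, each with a final run of 1. (2×1)/(2×2) = 1/2.
- *b* = 4: 6 orders, 2 with a run of 2 and 4 with a run of 1. (2×2 + 4×1)/(6×4) = 8/24 = 1/3.
- *b* = 6: 20 orders, with 2, 6 and 12 having runs of 3, 2 and 1. (6 + 12 + 12)/(20×6) = 30/120 = 1/4.
- *b* = 8: 70 orders, with 2, 8, 20 and 40 having runs of 4, 3, 2 and 1. (8 + 24 + 40 + 40)/(70×8) = 112/560 = 1/5.

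All four agree with the closed form 2/(*b* + 2).

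The best guess names the arm with more slots left and tosses a coin when they are equal. For *b* = 4 the chances of being right at the four positions are 1/2, 2/3, 2/3 and 1, averaging 2.833/4 = 0.708. Exact enumeration gives the other sizes.

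| Assumed block size | Certain in advance | Best guess correct | Expected certain among 44 |
|---|---|---|---|
| 2 | 50% | 75% | 22 blocks × 1 = 22 |
| 4 | 33% | 71% | 11 blocks × 4/3 = 14.7 |
| 6 | 25% | 68% | 7 full blocks × 1.5 = 10.5 |
| 8 | 20% | 67% | 5 full blocks × 1.6 = 8 |

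For blocks of 6 and 8, the 2 and 4 participants in the last, incomplete block add none, because certainty cannot arise in the first half of a block. With full concealment, 50% of guesses would be right and none would be certain.

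**The case against.** A reader might infer that concealment is absent, or that a physiatrist holding the list knows every assignment. The article does not support either. It describes an automatic system meant to conceal the allocation, mentions consent before assignment, and has the sequence converted into a list of participants, which can be read as people already enrolled and numbered. Assignment by the physiatrists could mean running the software after consent. Nothing says that upcoming allocations are visible before eligibility is decided. This objection stands: the fault is a role overlap at odds with the concealment claim, not proof that concealment is missing.

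The predictability figures are also conditional. They need a fixed block size that the physiatrist knows, together with knowledge of all past allocations. They would not hold as stated if the size were unknown to the physiatrist. That stands too, which is why a range is shown and not only the smallest blocks.

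On blinding, it can fairly be said that the Participants section discloses the true position, that nobody can be unaware of training on a robot, and that there are mitigations. Participants are not told the hypothesis, and the forms are handed out and checked by someone outside the rest of the study. So this is not a total lack of blinding, and the PI and analyst remain blind. But the mitigations do not make self-report blind, and disclosure in one section does not make the label in another correct.

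**Conclusion.** The blinding half holds outright: the double-blind label is contradicted by the article's own text, and the self-reported primary outcome is assessed unblinded. This rests on no assumption.

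The allocation half holds in a limited form. The claimed concealment is undermined because those who evaluate and enrol also assign and convert the sequence. Whether they see upcoming allocations is left open. If they know only past allocations and the block size, between 20% (blocks of 8) and 50% (blocks of 2) of allocations would be certain in advance, roughly 8 to 22 of 44 participants. Those numbers illustrate the exposure under assumed block sizes; they do not estimate bias that will occur.

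**What to change.** 1. **Allocation.** In the Participants section, state that once eligibility and consent are locked, the existing software releases each assignment, one at a time, directly to the treating physiotherapists and psychologist. The enrolling physiatrists should not handle the sequence or the running list. Do not route assignments through the secretarial staff: under Secondary outcome measure they hand out and check the questionnaires and contact participants at follow-up, so giving them allocations would open a new route for bias.
2. **Label.** Under Trial design and study setting, replace double-blind with *open-label, with PI and data analyst blinded*, and state that the self-reported outcomes are unblinded.
3. **If recruitment has begun,** record the procedure actually used for participants already allocated.

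The cost is a changed recipient for the software output, some wording, and a less favourable design label. No extra staff or participants are needed. In a single hospital with unblinded therapists, physiatrists may still hear of past allocations informally, so rerouting narrows the exposure without guaranteeing its removal.

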### Intervention description

The interventions will be performed by two physiotherapists with equal experience (i.e., 10 to 15 years experience in lymphedema rehabilitation). Before the study begins, they will receive adequate training from the physiatrists, each one responsible for one of the two arms of the trial. Following the Italian National Health System protocols on physiotherapy sessions, 30 physical training sessions of 60 min three times per week for 10 weeks will be programmed. At the end of the treatment, participants will be also asked to rate the effectiveness of the treatment using the 5-point Likert Global Perceived Effect (GPE) scale (1 = helped a lot, 2 = helped, 3 = helped only a little, 4 = did not help, 5 = made things worse) [18]. During the program intervention, no other treatment will be performed (e.g., physical modalities, drug therapies for lymphedema), while family doctors will be asked to avoid referring participants to other visits and/or other treatments. Using a specific form, the individuals will be asked to report any serious symptoms they might have during the trial. Participants will be inquired during each session and at the follow-up about their satisfaction with the program intervention; any reasons for skipping the program, seeking additional care, or taking medications to control pain will be discussed. In case of a condition that precludes further participation in the trial or the loss of eligibility (e.g., serious adverse events or other complications; persons with poor compliance that are unable to complete the entire set of exercises; people unable to continue with the clinical trial and request the investigator to withdraw), the participant will be discontinued from trial participation with full disclosure of the reasons and the principal investigator could be informed.

### Robot-assisted Rehabilitation Program (RRP)

The RRP will include robot-assisted exercises for upper-limb muscle isotonic and isometric strengthening (i.e., rotator cuff, thoraco-appendicular, scapulo-humeral, elbow, wrist, and hand muscles) and assisted mobilization of the shoulder (scapula-humeral) and the elbow, along with regular rehabilitation.

In particular, a planar robotic system (iCONE, Heaxel srl, Milan, Italy), already used in previous research on stroke population [17], will be used. This medical device for robot-assisted upper limb rehabilitation incorporates interactive exergames that require coordinated shoulder and elbow movements to perform planar reaching tasks displayed on a monitor. The device administers protocols based on intensive therapeutic exercise repetitions, guiding participants to specific points on the display, so that users receive real-time visual feedback on their position and movement accuracy.

The RRP will last for 60 h in total as a result of the presence of the robot-assisted exercises added to regular rehabilitation (described below).

### Regular rehabilitation

It will include simultaneously: (i) manual lymphatic drainage massage; (ii) elastocompressive therapy; and (iii) exercises for the head, neck, and upper-limb muscle isotonic and isometric strengthening (i.e., rotator cuff, thoraco-appendicular, scapulo-humeral, elbow, wrist and hand muscles), regional stretching (i.e., shoulder girdle and upper limb muscles), and assisted mobilization of the temporo-mandibular, shoulder, elbow, wrist, and hand joints [19].

The general program interventions will last for 30 h in total.

### Outcomes

#### Primary outcome measure

The primary outcome measure will be the change from the baseline of the Function domain in the Lymphedema Quality of Life (LYMQOL) questionnaire [20, 21] at 10 weeks and after 6 months. The LYMQOL is a self-administered questionnaire consisting of 21 items. The first 20 items assess the impact of lymphedema on Health-Related Quality of Life (HRQoL) and are categorized into four domains: Function (items #1–3), Appearance (items #4–8), Symptoms (items #9–14), and Mood (items #15–20). Each item is rated on a 4-point scale, ranging from 1 (not at all) to 4 (a lot), with higher scores indicating lower HRQoL.

The scores of all items within that domain are summed and divided by the total number of questions answered, in order to calculate the total score for each domain. Additionally, item #21 assesses the overall HRQoL, using an 11-point numerical scale ranging from 0 (poor HRQoL) to 10 (excellent HRQoL). The four summary scores related to each domain will be computed according to the guidelines provided by Keeley and colleagues [20].

### Participant timeline

The participant timeline is shown in Fig. 1.

**Fig. 1 Fig1:**
[figure not shown]
Schedule of enrolment, interventions, and assessments. LYMQOL, Lymphedema Quality of Life; NRS, Numerical Rating Scale; CFPDI-I, Craniofacial Pain Disability Inventory

### Data collection and management

The data collection and analysis processes will be conducted by the PI and biostatistician, respectively. Compliance with the European Regulation on the Protection of Personal Data (GDPR 2016/679) will be ensured, specifically with regard to the principles applicable to the processing of personal data (Article 5), lawfulness of processing (Article 6), and conditions for consent (Article 7).

All collected data will be used solely for scientific research purposes and will be securely stored to prevent unauthorized access. Measures will be taken to remove any information that could potentially identify the participants, ensuring their anonymity. Each participant will be assigned a unique identification number, which will be used in the dataset. The responsibility for keeping the data will lie with the principal investigator.

